## Abstract

**Background:**

Continuous subcutaneous insulin infusion (CSII) treatment among children with type 1 diabetes is increasing in Sweden. However, studies evaluating glycaemic control in children using CSII show inconsistent results. The distribution of responsibility for diabetes self-management between children and parents is often unclear and needs clarification. There is much published support for continued parental involvement and shared diabetes management during adolescence. Guided Self-Determination (GSD) is an empowerment-based, person-centred, reflection and problem solving method intended to guide the patient to become self-sufficient and develop life skills for managing difficulties in diabetes self-management. This method has been adapted for adolescents and parents as Guided Self-Determination-Young (GSD-Y). This study aims to evaluate the effect of an intervention with GSD-Y in groups of adolescents starting on insulin pumps and their parents on diabetes-related family conflicts, perceived health and quality of life (QoL), and metabolic control. Here, we describe the protocol and plans for study enrolment.

**Methods/design:**

This study is designed as a randomized, controlled, prospective, multicentre study. Eighty patients between 12–18 years of age who are planning to start CSII will be included. All adolescents and their parents will receive standard insulin pump training. The education intervention will be conducted when CSII is to be started and at four appointments in the first 4 months after starting CSII. The primary outcome is haemoglobin A1c levels. Secondary outcomes are perceived health and QoL, frequency of blood glucose self-monitoring and bolus doses, and usage of carbohydrate counting. The following instruments will be used: Disabkids, ‘Check your health’, the Diabetes Family Conflict Scale and the Swedish Diabetes Empowerment Scale. Outcomes will be evaluated within and between groups by comparing data at baseline, and at 6 and 12 months after starting treatment.

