
**Table 2 T2:** Data collection

**Before starting CSII**	• HbA1c, height, weight, insulin requirement, mean frequency of self-monitoring of blood glucose (SMBG)
	• ‘Check your health’, Disabkids, DFCS, Swe-DES 23 and treatment satisfaction.
**6 and 12 months after starting CSII**	• Same measures as before starting CSII
	• Frequency of bolus doses and usage of carbohydrate counting

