### Statistical analysis and power calculation

To detect a difference of 6 mmol/mol in HbA1c (SD: ± 9.1), at least 37 participants are required in each group (power 80% and alpha 0.05). SD is calculated from the available participants in the actual clinics (n = 160) at study start, mean HbA1c: 74.2 ± 9.1 mmol/mol. Allowing for patient withdrawals and those lost to follow up, 80 patients will be included in the study. All analysis will be conducted on an intention-to-treat basis. The differences between the groups will be analysed using an un-paired t-test with a 95% confidence interval and p < 0.05 considered as significant. A repeated measures ANOVA will be used for before and after comparisons in the groups, using the same confidence interval and level of significance. When testing differences between groups using Disabkids, ‘Check your health’, DFCS and Swe-DES 23, the same statistical analysis will be used.

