## Discussion

The aim of our study is to provide an educational program in an urban area, and its success depends on how well the study participants represent the population of interest. Previous studies have indicated that children with many diabetes-related conflicts have poorer glycaemic control, and thus, it is important that this group be represented in the study sample [27]. We have chosen to use HbA1c measured at the visit before the planned start of CSII as the inclusion criterion. An alternative, which is common in studies with adults, is to use a mean result from three HbA1c tests taken in the last year. We did not use this latter method as part of the entry criteria because some of the potential patients will have been diagnosed with diabetes for only a short time, and there is a risk of using an HbA1c result from a remission period. GSD is an empowerment-based program, and we have thus chosen to use Swe-DES 23, which is sensitive to change. Previous studies show that unclear responsibility distribution can explain omitted bolus doses and family conflicts, and we will also use DFCS, which is one of the most widely used measures of diabetes-specific family conflict [21,27]. To detect changes in perceived physical and emotional health, social relationships, general QoL and the burden of diabetes, we will use the measures Disabkids and ‘Check your health’ [33-35]. There is a risk that there will be high scores on perceived QoL already at baseline, but it is important to detect both rates of deterioration and improvement. We also want to observe any changes in the burden of diabetes. We will measure treatment satisfaction with one question; we have used this question in previous studies and it has been shown to be sufficient for measuring treatment satisfaction [18]. The intervention will take 4 months and evaluation with measurements of perceived QoL will be performed at baseline, 6 and 12 months to allow comparisons and to determine any changes. Previous research has shown that there is an initial improvement in the first months after the start of treatment using an insulin pump, which later subsides [14,16]. We believe that starting an insulin pump together with an empowerment-based, person-centred education model leads to retention of improved glycaemic control, QoL, responsibility distribution and reduced diabetes-related conflicts in the family.

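### HbA1c is the primary outcome without a primary time point, although it is compared between arms at 6 and 12 months and the power calculation covers one comparison

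*Protocol article*

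**What the plan says.** The Abstract (Methods/design) states "The primary outcome is haemoglobin A1c levels", with no visit attached. The same paragraph ends: "Outcomes will be evaluated within and between groups by comparing data at baseline, and at 6 and 12 months after starting treatment". Table 2, under Measures and data collection, schedules the baseline measures, HbA1c among them, again at "6 and 12 months after starting CSII".

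Under Statistical analysis and power calculation, differences between the groups are to be analysed by an "un-paired t-test with a 95% confidence interval and p < 0.05 considered as significant". The other method has a different job: "A repeated measures ANOVA will be used for before and after comparisons in the groups". The sample size there is 37 per group for a difference of 6 mmol/mol with SD 9.1, power 80% and alpha 0.05. It also names no visit.

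On purpose, the Discussion reports from previous research that "there is an initial improvement in the first months after the start of treatment using an insulin pump, which later subsides". It then gives the investigators' belief that combining pump start with the education model "leads to retention of improved glycaemic control, QoL, responsibility distribution and reduced diabetes-related conflicts in the family". The Discussion part of the Abstract presents retention as what the study is to determine. The section Study aim and hypothesis is less specific: it refers to improved metabolic control, without a time point and without mention of retention.

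**The concern.** A primary outcome is fully fixed only when the visit is fixed. Here there are two candidate visits, one test and one significance level, and no rule that joins them. No primary visit, testing order, alpha split or requirement that both visits succeed is stated. The repeated measures ANOVA is assigned to before-after comparisons in the groups, so it does not serve as one overall between-arm test that would settle the matter.

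Two things are at stake. First, if either visit may carry the primary claim, the false-positive rate exceeds the 5% on which the sample size rests. Second, the visit determines which question is answered. The intervention ends about 4 months after pump start, so month 6 falls about two months after its end (6 − 4 = 2). An arm difference there that has gone by month 12 would not show retention, yet nothing in the text would stop it from being reported as a positive primary result.

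**Working it through.** **Inputs from the protocol article.** Difference 6 mmol/mol, SD 9.1, power 80%, alpha 0.05, 37 per group, 80 in total (Statistical analysis and power calculation). The 95% confidence interval implies a two-sided test. HbA1c is compared at 6 and 12 months (Abstract; Table 2).

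**Assumed.** The correlation ρ between the 6- and 12-month test statistics is not given, so a range of 0.5 to 0.9 is shown. SD 9.1 is taken to apply at each visit. Participants are treated as independent.

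**Step 1: reproduce the sample size.** n per group = 2 × (z₀.₉₇₅ + z₀.₈₀)² × SD² / difference² = 2 × (1.960 + 0.842)² × 82.81 / 36 ≈ 36.1, rounded up to 37. The exact t-test calculation gives 37.1, with power 79.9% at 37 per group. The stated figure is right for one comparison, at one visit, at undivided alpha.

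**Step 2: false-positive rate if either visit suffices.** With no true effect at either visit, the chance of at least one significant result is 1 − P(|Z₁| ≤ 1.96 and |Z₂| ≤ 1.96), where Z₁ and Z₂ are bivariate normal with correlation ρ. For ρ = 0 this is 1 − 0.95² = 9.75%.

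| ρ (assumed) | Either direction | Favouring the intervention only |
|---|---|---|
| 0.5 | 9.07% | 4.54% |
| 0.7 | 8.35% | 4.17% |
| 0.8 | 7.81% | 3.90% |
| 0.9 | 7.04% | 3.52% |
| Nominal, one test | 5% | 2.5% |

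The rate is above nominal at every correlation below 1.

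**Step 3: how easily a 6-month-only result arises.** Suppose the true difference is 6 mmol/mol at 6 months and zero at 12. The 6-month statistic then has mean 6 / (9.1 × √(2/37)) ≈ 2.84. The chance that month 6 is significant in favour of the intervention and month 12 is not comes to about 78% (37 per group, simulated for ρ of 0.5 to 0.8, with almost no dependence on ρ).

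**Step 4: what the remedies do to the sample size.**
- One primary visit: alpha stays 0.05, 37 per group stands, and the total stays 80.
- Both visits kept, either sufficient, 0.025 each: n = 2 × (2.241 + 0.842)² × 82.81 / 36 ≈ 43.7, so 44 per group by the normal approximation. The t-test gives 45.01, so 46. At 37 per group the power per visit would be 70.7% by the t-test (72.4% by the normal approximation).

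**The case against.** The best defence is that the article does not say what a critic may read into it. A reader might infer that HbA1c is declared primary at both visits, each a separate route to success. The text does not say that: it gives an outcome, a set of visits and a test, and leaves open how they combine. The 7% to 9% therefore applies only if either visit is allowed to count. This stands, and the point is worded accordingly.

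A reader might also infer that the formal hypothesis is retention. It is not. Study aim and hypothesis says only that metabolic control will improve, and an effect at 6 months would be consistent with that. Retention is the stated purpose in the Abstract's Discussion and a belief in the main Discussion.

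Nor does the remark that early pump benefit fades invalidate a 6-month comparison. Both arms start the pump, so a passing pump effect is common to both and does not by itself produce an arm difference. The remark supports interest in month 12 and no more.

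A larger inflation might be inferred by adding the effect of randomizing groups rather than individuals. The article gives no intracluster correlation or design effect, that is a separate matter, and naming a visit would not cure it. It is left out of the figures here.

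Finally, testing order and multiplicity rules are often left to a statistical analysis plan, which is not shown. That is fair for the detail. It does not cover the primary visit itself, because the power calculation printed in the article depends on which comparison it is for.

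**Conclusion.** The point holds in this form: the primary visit is not named, two between-arm comparisons of the primary outcome are planned at p < 0.05, and the sample size fits one of them. If either may count as success, the two-sided false-positive rate is about 7% to 9% instead of 5%, or about 3.5% to 4.5% instead of 2.5% for errors favouring the intervention. These figures rest on assumed correlations of 0.9 to 0.5 and on independent participants. The inflation is moderate. The more important consequence is that an effect lost by 12 months could be presented as the primary result of a trial whose stated purpose is retention. The sample size arithmetic itself is correct. The change should be made, but the gap does not by itself invalidate the design.

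**What to change.** State in the protocol that the single primary endpoint is the between-arm difference in HbA1c at 12 months after pump start, tested at two-sided 0.05. Say that the power calculation (6 mmol/mol, SD 9.1, 37 per group) refers to that comparison. Make HbA1c at 6 months secondary, either reported as an estimate with its confidence interval or tested only if the 12-month result is significant.

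The cost is about a sentence. The total of 80, the visits and the measurements are unchanged. The downside is that an effect seen at 6 months alone can no longer be claimed as the primary result. If the sponsor wants to keep that claim, an alpha split is the alternative, but at 0.025 per visit it needs 46 per group by the t-test before any allowance for withdrawals, against 37 now. Naming 12 months is cheaper and closer to the stated purpose.

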**Discussion:**

In this study, we will assess the effect of starting an CSII together with the model of GSD to determine whether this approach leads to retention of improved glycaemic control, QoL, responsibility distribution and reduced diabetes-related conflicts in the family.

**Trial registration:**

Current controlled trials: ISRCTN22444034

## Background

### Diabetes

Type 1 diabetes is the most predominant form of diabetes among children in Sweden. The most common treatment is multiple daily injections (MDI), but treatment with continuous subcutaneous insulin infusion (CSII) is an alternative that is being used more frequently. In 2011, 42% of the children with type 1 diabetes in Sweden were treated using CSII [1]. In many children and adolescents, insulin requirements decrease transiently after they have been diagnosed with type 1 diabetes and insulin treatment has been initiated. The remission phase in type 1 diabetes is defined as an insulin requirement < 0.5 IU/kg with a haemoglobin A1c (HbA1c) of < 53 mmol/mol [2]. The recommended HbA1c target for children and adolescents is < 58 mmol/mol without increasing the number of hypoglycaemic episodes [2,3]. The Diabetes Control and Complications Trial (DCCT) and follow up data clearly indicate that poor glycaemic control during adolescence and young adulthood increases the risks of severe complications, such as nephropathy and retinopathy later in life [4,5]. In Sweden, there are clear, age-related differences in HbA1c results among young people with diabetes. After starting school (at age 7 years), HbA1c tends to increase with increasing age [6,7].

### Insulin pump treatment

CSII is currently the most physiological way to deliver insulin [8]. The clinical indications for starting CSII for children and adolescents are broad. Treatment with CSII is associated with an increased cost compared with MDI. However, some studies have shown that CSII is cost effective when it results in improved metabolic control and quality of life (QoL) [9-11]. Structured and intensive education on basic and specific requirements of insulin pump therapy is essential for the patient and their parents so that they become familiar with the pump and its features [12]. Studies evaluating glycaemic control in children using CSII have shown divergent results [13-17]. One explanation for deteriorated glycaemic control among adolescents treated with CSII is omitted bolus doses before meals [18,19]. This is mainly explained by loss of focus when the children forget to take their medication. The distribution of responsibility for diabetes self-management between children and parents is often unclear and needs to be clarified [20,21].

### Parental involvement

Adolescence is the period when responsibility for diabetes management should be transferred from the parents to the teenager [22]. There is much published support for continued parental involvement and shared diabetes management during adolescence [22-25]. Communication and family dynamic factors appear to be important variables for glycaemic outcomes in adolescents with diabetes. They are stronger predictors of glycaemic control than age, gender or insulin treatment regimen [26]. Adolescents starting CSII found coping with diabetes easier than adolescents using MDI, but there were no differences in QoL, depression and self-efficacy [16]. Viklund et al. showed that five categories are important for decision making competence: cognitive maturity, personal qualities, experience, social network and parental involvement. Teenagers describe how parental involvement can be constructive or destructive [24], and the challenge is to find a level that is comfortable for all involved [22]. Children who have many diabetes-related conflicts with parents have higher HbA1c compared with those who have fewer conflicts, and the quality of their relationships is a critical factor in diabetes self-management [27].

### GSD-Young

Self-management is an active and proactive process that involves activities and goals and that is continuously ongoing. It involves shared but shifting responsibility for diabetes care and decision making between the child and their parents, and it is a process that also involves health care staff. It is important to be aware that self-management may differ from one parent/child dyad to another [28]. Person-centred care highlights the importance of knowing the person behind the patient to engage the person as an active partner in his/her own care and treatment [29]. Guided self-determination (GSD) is an empowerment-based, person-centred, reflection and problem solving method intended to guide the patient to becoming self-determined and developing life skills to manage difficulties in diabetes self-management using worksheets. GSD helps the patient and the health care staff to overcome barriers to empowerment. It has been effective both in individual and group training of adults with type 1 diabetes [30]. [name] et al. have adapted GSD for adolescents and their parents as Guided self-determination-Young (GSD-Y) and there is an ongoing study of adolescents with type 1 diabetes in Denmark [31]. This study will evaluate the effect of an intervention using GSD-Y in groups of adolescents and their parents. It will be carried out at routine outpatient clinics.

### Study aim and hypothesis

The aim of this study is to evaluate whether an intervention with GSD-Y in groups of adolescents starting on insulin pumps and their parents leads to fewer diabetes-related family conflicts, increased perceived health and QoL and improved metabolic control.

We hypothesise that using GSD-Y in groups of adolescents and their parents will increase parental support, and that clarified distribution of responsibility may decrease the negative burden of diabetes, and improve perceived health, QoL and metabolic control among adolescents starting on continuous subcutaneous insulin infusion.

## Methods/design

### Study design and setting

This study is designed as a randomized, controlled, prospective, multicentre study. The study will be conducted at Astrid Lindgren’s Children’s Hospital, Karolinska University Hospital, Stockholm, Sweden and Sachs’ Children and Youth Hospital, Söderjukhuset, Stockholm, Sweden. These hospitals care for all of the children with type 1 diabetes in the region (1200 patients).

### Participants and recruitment

Eighty patients between 12 and 17.99 years who are planning to start CSII will be included. Patients will be excluded if their diabetes has been diagnosed within the past year, HbA1c is < 63 mmol/mol, insulin requirement is < 0.5 IU/kg, if the patient is using continuous glucose monitoring when they start CSII, or if the teenager or their parents have difficulties understanding Swedish. Approximately 4 times per year, information meetings about pump treatment and different insulin pump models will be held at the study sites. Oral and written information about the present study will be given to patients who fulfil the inclusion criteria. Written informed consent for participation in the study will be obtained from the parents and adolescents.

### Randomization

Adolescents and their parents who are willing to participate in the study will be divided consecutively into groups depending on which pump model they have chosen. The groups will then be randomized to either intervention or control. The main reason for group randomization is to make the study feasible within a reasonable time. It is not possible to provide enough staff to start different pump models at the same time. Our experience indicates that there are no differences in distribution between the sexes among those starting CSII; therefore, we have not stratified for gender.

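### Pump model is fixed within each randomised group, yet neither the described allocation nor the planned t-test takes account of it

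*Protocol article*

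**What the plan says.** The Randomization section forms groups by pump choice: participants "will be divided consecutively into groups depending on which pump model they have chosen". It continues: "The groups will then be randomized to either intervention or control". The reason given for single-model groups is staffing: "It is not possible to provide enough staff to start different pump models at the same time". The only remark on stratification concerns sex. In the authors' experience the sexes are equally distributed among pump starters, "therefore, we have not stratified for gender".

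The study runs at two Stockholm hospitals (Study design and setting). The section on statistical analysis and power calculation sets the target: "To detect a difference of 6 mmol/mol in HbA1c (SD: ± 9.1"), with at least 37 per arm for 80% power at alpha 0.05. It then adds: "Allowing for patient withdrawals and those lost to follow up, 80 patients will be included in the study". Arms are compared with an unpaired t-test, and no term for pump model, start group or hospital is mentioned.

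**The concern.** When a characteristic varies within randomised units, randomising many people tends to even it out. When it is constant within a unit, only the number of units helps, and here that number is 80 divided by the group size. The design ties pump model to the unit of randomisation, so the arms can easily end up with different mixes of models. Any difference between models in later HbA1c would then be mixed with the GSD-Y effect. A baseline HbA1c comparison would not show it, because such a difference would arise only after pump start. The planned t-test neither adjusts for model nor recognises the group.

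The stated reason for not stratifying by sex is also weak. An even split among pump starters does not ensure balance between arms; chance imbalance in a two-level factor is in fact greatest at an even split. This is minor, because sex can vary within a group.

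**Working it through.** **1. The plan's own figure.** Inputs from the power calculation: difference 6, SD 9.1, power 80%, alpha 0.05 (sidedness is not stated; two-sided is used).

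n per arm = 2 × (1.960 + 0.842)² × 9.1² / 6² = 2 × 7.85 × 82.81 / 36 ≈ 36.1, rounded up to 37.

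The t-based solution is 37.1. The stated 37 reproduces, and nothing below disputes it.

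**2. Assumptions.** The article does not give the number of groups, their size, the number of models or their popularity. Assumed: 80 patients in equal groups of 4, 5, 8 or 10 (K = 20, 16, 10 or 8 groups), half the groups in each arm, and two models each covering half the groups.

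**3. Chance of imbalance.** With K/2 groups of model A and K/2 groups per arm, the probability that the intervention arm holds a groups of model A is

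C(K/2, a) × C(K/2, K/2 − a) / C(K, K/2).

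The difference in model share between arms is |2a − K/2| / (K/2). Probability of a difference of 40 points or more:

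- K = 20: 1 − (63,504 + 2 × 44,100)/184,756 = 17.9%
- K = 16: 1 − (4,900 + 2 × 3,136)/12,870 = 13.2%
- K = 10: 1 − (2 × 100)/252 = 20.6%
- K = 8: 1 − 36/70 = 48.6%
- 80 individuals: 0.1%

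The series is not monotone because only certain differences can occur. The smallest one at or above 40 points is 40 for K = 20, 50 for K = 16, 60 for K = 10 and 50 for K = 8. With a nominal 30:70 share of models, the range over the same group counts is about 3% to 43%.

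**4. SD of the imbalance.** For equal shares it is 1/√(K − 1): 0.229 (K = 20), 0.258 (16), 0.333 (10) and 0.378 (8), against 0.113 for 80 individuals.

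**5. Effect on the estimate.** At 40 per arm the standard error is 9.1 × √(2/40) = 2.03 mmol/mol, with variance 4.14. Assume the models differ by 3 mmol/mol; the documents give no such figure. The added variance is (3 × SD of imbalance)²:

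- K = 20: 0.47; SE = √4.61 = 2.15, up 6%
- K = 16: 0.60; SE = √4.74 = 2.18, up 7%
- K = 10: 1.00; SE = √5.14 = 2.27, up 11%
- K = 8: 1.29; SE = √5.43 = 2.33, up 15%
- 80 individuals: 0.11; SE = √4.26 = 2.06, up 1%

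In a single trial with a 50-point imbalance, the estimate would shift by 0.5 × 3 = 1.5 mmol/mol. That is a quarter of the target difference, or about 0.7 of a standard error (1.5/2.03).

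**The case against.** Several objections have force.

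- **Silence.** Only stratification by sex is expressly ruled out. A condensed article may leave blocking or other restrictions to the full protocol. A reader might infer that the groups are definitely randomised without regard to pump model; the text supports only that none is described. What stands is that the article itself states single-model groups and a t-test without adjustment.
- **Few groups.** This is an assumption, as is any HbA1c difference between models. Both arms receive the standard pump training.
- **Hospital.** A reader might extend the argument to site. That requires each group to come from one hospital, and the article does not say so. It says only: "Approximately 4 times per year, information meetings about pump treatment and different insulin pump models will be held at the study sites". The site version is not established.
- **Arm sizes.** A reader might also infer that the trial is likely to miss 37 per arm. Under unrestricted allocation of 10, 16 or 20 groups, both arms reach 37 of 80 in only 18% to 25% of cases. That is merely the chance of an exact 40/40 split. Power is about 83% at 40/40, 82% at 35/45 and 81% at 32/48, so this is not a defect.
- **Bias.** Randomisation stays valid on average. The imbalance adds variance and can confound a particular realised trial, but it does not push the estimate systematically in either direction.
- **Stratification has a price.** With perhaps 10 to 16 groups, crossing model with hospital could leave cells of one or two groups, and several fixed effects would use scarce degrees of freedom. This argues against double stratification, but not against stratifying by the one factor that defines the groups.

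**Conclusion.** The point holds in a limited form. By the article's own description, pump model is constant within each randomised group, no stratification by it is described, and the t-test has no term for model or group. With 8 to 20 groups and two equally popular models (all assumed), a gap of 40 or more points between arms occurs in about 13% to 49% of allocations, against about 0.1% under individual randomisation. The loss of precision, about 6% to 15% in the standard error, depends on a further assumed 3 mmol/mol difference between models; if the models perform alike, there is none from this source. This is a cheap, worthwhile improvement to allocation and analysis. It is not evidence of bias or of a wrong sample-size calculation.

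**What to change.** **Allocation.** Randomise start groups within pump model, in blocks of varied size, once consent and group membership are fixed. Pool rare models into one stratum. If the full protocol already does this, the article should say so.

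**Analysis.** Replace the unpaired t-test for HbA1c with a model that has a pump-model term and accounts for start group, by a random group effect or a group-level analysis. A pump-model term alone would not deal with correlation within groups. Adjustment alone also recovers less than stratification: with equal shares and a realised 50-point gap, arm and model correlate at 0.5, so the variance of the adjusted effect is multiplied by 1/(1 − 0.5²) = 1.33.

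**Hospital.** Record it, and use it as a covariate only if groups are formed within one hospital and numbers allow.

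**Sex.** Remove the argument that an even split among pump starters makes stratification unnecessary.

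**Cost.** A new allocation list and a short change of text. Blocks may stay incomplete for rare models, and the last allocation in a block may be guessable; varied block size and prior consent limit this. The analysis gives up a few group-level degrees of freedom. With two models, a group-level analysis keeps 16 − 3 = 13 with 16 groups, but only 8 − 3 = 5 with 8.

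### An even sex mix among pump starters is no reason to ignore sex in allocation, and the between-arm t-test adjusts for neither sex nor age; the cost is modest precision and credibility, not bias

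*Protocol article*

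**What the plan says.** All places are in the protocol article.

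- **Randomization.** Families are "divided consecutively into groups depending on which pump model they have chosen". Then: "The groups will then be randomized to either intervention or control". On sex: "Our experience indicates that there are no differences in distribution between the sexes among those starting CSII; therefore, we have not stratified for gender". No other balancing factor is mentioned, and the number and size of groups are not given.
- **Participants and recruitment.** "Eighty patients between 12 and 17.99 years who are planning to start CSII will be included".
- **Background, Diabetes.** "In Sweden, there are clear, age-related differences in HbA1c results among young people with diabetes", followed by: "After starting school (at age 7 years), HbA1c tends to increase with increasing age".
- **Background, Parental involvement.** Of communication and family factors: "They are stronger predictors of glycaemic control than age, gender or insulin treatment regimen".
- **Statistical analysis and power calculation.** "The differences between the groups will be analysed using an un-paired t-test". The same analysis is to be used for the four questionnaires. Repeated measures ANOVA is assigned to the before-and-after comparisons. No covariate is named for either method.

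**The concern.** The protocol gives a reason for leaving sex out of the allocation, and the reason fails. Whether a factor deserves balancing or adjustment depends on whether it predicts the outcome. How common each sex is among recruits does not answer that. Nor does an even mix overall protect against an uneven split between two arms of about 40.

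Age is the factor for which the document itself reports a relation to HbA1c, the primary outcome. Both factors are known for every member of a group before that group is randomised, because groups are formed first and allocated afterwards. The stated test uses neither.

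Whole groups are randomised, so there are fewer than 80 units over which differences can even out. If members of a group resemble each other in age or sex, visible gaps between arms become more likely. A reader of the results would then have an unadjusted comparison and no pre-specified adjusted one to set beside it. Whatever outcome variance age or sex explains also stays in the error term.

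**Working it through.** **1. The plan's own figure.** Difference 6 mmol/mol, SD 9.1, power 80%, alpha 0.05 (two-sided assumed):

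n per arm = 2 × (1.960 + 0.842)² × 9.1² / 6² = 36.1, rounded up to 37. The t-based solution is 37.1, and power at 37 per arm is 79.9%. The stated 37 reproduces. It does not depend on age or sex, and this point does not change it.

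**2. Assumptions for what follows.** 40 per arm (half of the stated 80), 50% girls, age uniform over 12 to 18. The document gives neither the sex share nor the age distribution.

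**3. Chance gap in sex, no clustering.**
- Normal approximation: SD of the gap = 0.5 × √(2/40) = 0.112, and P(gap ≥ 20 points) = 7.4%.
- Simulation of independent patients: 9.4%.
- Exactly 40 girls among 80, split 40:40 (hypergeometric): SD 11.25 points, P = 11.7%.

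The range is therefore about 7-12%, even with a perfectly even mix overall.

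**4. Chance gap in mean age, no clustering.**
- SD of age = 6/√12 = 1.73 years.
- SD of the gap in means = 1.73 × √(2/40) = 0.387 years.
- P(gap ≥ 0.5 years) = 2 × (1 − Φ(0.5/0.387)) = 19.7%.
- P(gap ≥ 1 year) = 1.0%.

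**5. Sensitivity to group randomisation.** With random group membership these probabilities do not change. If members of a group resemble each other, the variance of the gap is multiplied by 1 + (m − 1) × ICC. For assumed groups of 5 to 8 and an assumed ICC of 0.1 to 0.2, the chance of a sex gap of 20 points or more is 13-25%, and of an age gap of half a year or more 28-40%.

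**6. What an age gap is worth.** The slope of HbA1c on age is assumed, because the document gives none. The shift is 0.5 years × slope. The share of variance explained is R² = (slope × 1.73)² / 9.1². The adjusted SD is 9.1 × √(1 − R²).

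| Assumed slope (mmol/mol per year) | Shift for a 0.5-year gap | Share of the planned 6 | R² | Power at 37 per arm, age-adjusted |
|---|---|---|---|---|
| 0.5 | 0.25 | 4% | 0.9% | 80.3% |
| 1 | 0.5 | 8% | 3.6% | 81.3% |
| 2 | 1.0 | 17% | 14.5% | 85.7% |

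Unadjusted power is 79.9%. The last column is an upper bound on the gain: it ignores clustering and assumes that no other covariate, such as baseline HbA1c, has already absorbed the age effect.

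**7. Scale.** The standard error of the arm difference at 40 per arm, without clustering, is 9.1 × √(2/40) = 2.03 mmol/mol. The shifts in the table are 0.12 to 0.49 of that.

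**8. Sex.** No corresponding row can be written, because nothing in the document gives an effect of sex on HbA1c.

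**The case against.** The strongest reply is that leaving sex unstratified is no error. Stratification is optional, and randomisation makes the comparison unbiased whatever split occurs. The SD of 9.1 comes from 160 available patients in these clinics, so it already contains whatever variation age and sex contribute. A half-year age gap therefore lies within the 2.03 mmol/mol standard error and is not added to it. All of this stands.

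A reader might infer that the arms will be confounded by sex because the Parental involvement section lists gender among the predictors of glycaemic control. The text does not support that. It ranks family factors above age and gender and gives no size for either, which is compatible with a negligible sex effect.

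A reader might also infer that age drives HbA1c in this sample. The text says only that HbA1c tends to rise with age after school start. The trial covers a six-year band and excludes patients with HbA1c below 63 mmol/mol, which would be expected to flatten any slope. This stands too, and it is why the slope range starts at 0.5.

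Finally, the article is condensed, and further covariates may sit in a fuller document. That answers the silence about balancing on age. It does not answer the stated rationale, which is wrong as written, or the named test, which cannot adjust and would have to be replaced.

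**Conclusion.** The rationale for not stratifying by sex is a non sequitur, and the stated between-arm test uses neither age nor sex although both are known before allocation. The consequence is modest. Noticeable gaps are plausible: about 7-12% for 20 points or more on sex and about 20% for half a year or more on mean age, without clustering. Such an age gap would be worth 0.25-1.0 mmol/mol, with age explaining roughly 1-14% of the HbA1c variance.

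These figures rest on assumed values for the sex share, age distribution and slope; the clustered figures also rest on assumed group sizes and ICCs. The tempting stronger conclusion, that the result will be biased or that stratification was required, does not follow. The loss is in precision and in how convincing the comparison will look if the arms differ visibly.

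**What to change.** 1. In Randomization, delete the inference from the sex mix of pump starters. It is enough to say that allocation is not stratified by sex.
2. In Statistical analysis and power calculation, replace the unadjusted t-test with a pre-specified between-arm model for HbA1c and for each questionnaire score. The model should include age, sex and the baseline value of the outcome, and should account for the randomised groups.

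The cost is a few degrees of freedom, two of them for age and sex. Age and sex are known at entry, and the baseline values are already collected before CSII starts, so no new patients, staff or data are needed.

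Balancing the allocation itself on age and sex is optional and not part of this fix. Groups form consecutively, so constrained randomisation, which needs all groups known in advance, fits poorly. Minimising a small number of visible groups on two factors could make allocation predictable.
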